### Adverse events (AE) and safety evaluation

Safety is assessed by registering any adverse events suffered by the patients in the intervention group that could potentially be secondary to the physical exercise performed during the training sessions.

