### Participants and eligibility

Patients are admitted to the hospital, to the Medical Oncology Department, regardless of the type of cancer, and usually in relation to complications related to their underlying disease or related treatments. Patients or their relatives (if the patient is unable to comprehend themselves) are informed of the random inclusion in one group but are not be informed which group the patient belongs to. The data for both the intervention group and the control group will be obtained at three different times: at baseline, before discharge, and at the 1-month followup.

The inclusion criteria are: age 65 years or older, Barthel Index score of 60 or more (scale, 0 [severe functional dependence] to 100 [functional independence]), being able to ambulate (with/without assistance), and to communicate and collaborate with the research team, and signing the informed consent form,. The exclusion criteria included are expected length of stay less than 6 days or more, terminal illness, very severe cognitive decline (ie, Global Deterioration Scale score, 7), uncontrolled arrhythmias, acute pulmonary embolism, acute myocardial infarction, and extremity bone fracture in the past 3 months. Inclusion and exclusion criteria are summarized in Table 1.

**Table 1 Tab1:** Eligibility criteria

**Inclusion**	**Exclusion**
• Women and men aged ≥ 65 years	• Expected length of stay < 6 days
• Barthel Index ≥ 60 points	• Terminal illness
• Able to ambulate (with/without assistance)	• Very severe cognitive decline (i.e., GDS 7)
• Sign the informed consent	• Uncontrolled clinical situations as unstable infections, arrhythmias, acute pulmonary embolism, acute myocardial infarction or limb bone fracture in the past 3 months, or any clinical condition considered by the attending doctor as innapropriate for the trial.
• Able to communicate	

GDS: Global Deterioration Scale

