Basic sociodemographic and clinical data of the participants are collected in the baseline visit (Table 1). All adverse events, including those related exclusively to the exercise such as muscle pain, fatigue and general aches and pains, will be recorded in an “adverse events diary” during follow-up visits by the training and testing staff, and by self-report during the study period. The time at which different variables (primary and secondary) will be measured is detailed in Table 2. A blood sample will be taken on the days of the baseline and before discharge measurements.

The variables related to the tumor and the reason for, and evolution of admission will also be collected, distinguishing between toxicity due to chemotherapy (CTCAE v5.0), intercurrent medical complication, or neoplastic progression.

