In order to check the assumption that the potential impact of missing data is negligible (created by a missing complete at random or a missing not at-random mechanism), best–worst and wors`t-best case sensitivity analyses will be used. When the missing data surpasses 5% and if this is supported by the previous sensitivity analysis, a missing at-random mechanism will be assumed and missing values will be imputed using the R package MICE (Multivariate Imputation via Chained Equations). If the proportion of missing data is very large (rises over 40%) on important variables, trial results will be considered hypothesis-generating results.

We will compare the proportion or number of adverse events between groups, using chi-square test or Mann-Whitney U test.

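### The protocol gives two incompatible rules for collecting adverse events, and only one of them supports the planned between-group comparison

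*Protocol article*

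**What the plan says.** Three places in the protocol article bear on adverse events.

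- **Participants and eligibility** (text after Table 2): "All adverse events, including those related exclusively to the exercise such as muscle pain, fatigue and general aches and pains, will be recorded" in a diary, "during follow-up visits by the training and testing staff, and by self-report during the study period". Exercise-related complaints are a named subset of all events. No arm is singled out.
- **Adverse events (AE) and safety evaluation**, the only section devoted to safety: the assessment consists of "registering any adverse events suffered by the patients in the intervention group that could potentially be secondary to the physical exercise" done in the sessions. One arm is named, and events are filtered by possible cause. Nothing is said about controls.
- **Statistical procedures** (last sentence): "We will compare the proportion or number of adverse events between groups, using chi-square test or Mann-Whitney U test".

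The participants section also says in general terms, not specifically about adverse events: "The data for both the intervention group and the control group will be obtained at three different times".

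**The concern.** A between-group test of adverse events needs both arms observed under one definition, by the same means, over the same period. The participants section can supply that; the safety section cannot. The article does not say which section takes precedence, and staff looking for the safety rule would naturally turn to the section with that title.

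If they follow it, the control count is zero because nobody registered events there. Any registered difference then runs against the intervention, whatever the truth. The causality filter would also leave out of the intervention arm's count any event not linked to training, so the comparison could not show whether exercise adds events overall. No later analysis can recover control-arm events that were never recorded. The article describes the trial as recruiting, with about one-third of the target reached, so the rule matters now.

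**Working it through.** The article states no adverse event rate or count, so there is no figure of its own to reproduce. The check is a comparison of the texts, followed by an illustration of size.

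**1. The rules side by side**

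| Section | Events | Arms | Supports a between-group test? |
|---|---|---|---|
| Participants and eligibility | All, exercise-related as a subset | Not restricted | Yes, if applied alike in both arms |
| Adverse events (AE) and safety evaluation | Possibly due to the exercise | Intervention group named; controls not mentioned | No |
| Statistical procedures | Proportion or number of events | Both | Needs the first rule |

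**2. Inputs for the illustration**

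- 120 per group (Statistical procedures).
- 40 per group: one-third of the target (Discussion), 120/3 = 40.
- Significance level 0.05 (Statistical procedures), taken as two-sided.
- True event rates: assumed, and equal in both arms.
- Control count: 0, which holds only if the safety section governs.

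**3. Single outcomes at 120 per group**

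With x registered events against 0, the two-sided Fisher p is 2 × C(120, x)/C(240, x).

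- Assumed rate 5%, all registered: x = 0.05 × 120 = 6. p = 2 × (120·119·118·117·116·115)/(240·239·238·237·236·235) = 2 × 0.0147 = 0.03.
- Assumed rate 10%, all registered: x = 0.10 × 120 = 12. p = 2 × C(120, 12)/C(240, 12) = 0.0004.

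**4. How often the planned chi-square test would reject**

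With n per group and x versus 0, the uncorrected statistic reduces to 2n·x/(2n − x), with critical value 3.84.

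- n = 120: x = 3 gives 720/237 = 3.04; x = 4 gives 960/236 = 4.07.
- n = 40: x = 3 gives 240/77 = 3.12; x = 4 gives 320/76 = 4.21.

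So four registered events against none reject at either size. The rejection rate is the binomial probability of four or more. The last two columns give the same test with equal recording in both arms.

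| Registered rate | One arm only, 120 | One arm only, 40 | Both arms, 120 | Both arms, 40 |
|---|---|---|---|---|
| 2% | 22% | 1% | not run | not run |
| 5% | 86% | 14% | 4.8% | 4.3% |
| 10% | 99.8% | 58% | 5.2% | 5.9% |
| 20% | about 100% | 97% | 5.1% | 5.1% |

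**5. Allowing for the causality filter**

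The safety section would register only events possibly due to exercise. The registered rate is therefore the true rate times the attributed share. For a true rate of 10% at 120 per group:

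- Share one: 12 versus 0, p = 0.0004.
- Share one-half: 6 versus 0, p = 0.03.
- Share one-quarter: 3 versus 0, p = 2 × (120·119·118)/(240·239·238) = 0.25.

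The contradiction is certain from the text. Its numerical consequence depends on a share the article does not give.

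**The case against.** The strongest reply is that the article already provides for complete recording. The participants section covers all adverse events without limiting them to an arm, both groups are assessed at common times, and the statistical section fits that scheme. The safety section does not contain the word *only*, so it may simply describe an additional, exercise-specific assessment. Under equal recording the test behaves as it should, rejecting in about 5% of trials.

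Much of this stands, and it rules out several stronger inferences a reader might draw.

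- *Events are registered solely in the intervention arm, so the comparison is invalid by construction.* This follows only if the safety section overrides the participants section, which the article does not say.
- *Falls in exercising patients go uncaptured.* Table 2 schedules falls at T1 to T4 for each participant. Mortality and readmission are also secondary end points.
- *Unblinded staff judge causality before an event is recorded.* No section says who judges causality or in what order. The randomization section states that outcome assessors are blinded to allocation.
- *The p-values above measure the actual bias.* They assume every intervention-arm event is registered, whereas the safety section would admit a subset. A true excess of session-related events would also be no false signal, since controls have no sessions.

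What does not stand is the suggestion that nothing needs correcting, or that this is journal condensation. Nothing in the safety section marks it as an addition to general recording. Two stated rules conflict; this is not omitted detail. One question also remains open under the all-events rule: training staff are among the recorders, and they meet intervention patients twice a day for four days. The article describes no matching contact with controls, and does not settle whether ascertainment would be equal.

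**Conclusion.** Wrong as written. The article states two incompatible collection rules, and its between-group test is valid under only one of them, applied equally to both arms. If the safety section governs, the control arm contributes no events and the comparison is biased against the intervention by differential ascertainment.

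Under assumed equal rates of 5% to 10%, with all intervention-arm events registered and none in controls, the chi-square test would falsely reject in 86% to 99.8% of trials at 120 per group, and in 14% to 58% at 40 per group. These figures are illustrative and fall with the share of events attributed to exercise. The documents do not establish that control-arm events are in fact going unrecorded. The primary SPPB analysis is unaffected.

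**What to change.** Rewrite the safety section to agree with the participants and statistical sections:

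1. Record all adverse events, whatever the suspected cause, in both arms from randomisation to last follow-up, at the same visits and with the same questions. Name the last visit, since the participants text ends at 1 month and Table 2 at 3 months.
2. Use that set, and no other, for the between-group test.
3. Report session-related events, such as muscle pain from training, descriptively for the intervention arm only, outside the test.

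The diary and the visits already exist. The cost is a change of wording and slightly more recording in controls. If controls already enrolled were not asked about adverse events, the report should say so and say from when both arms were recorded alike.

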## Initial results

Patients show a mean age of 74.4 years (SD 5.3), mostly men (60%) and frail (Short Physical Performance Battery (SPPB)) around 8.5 (see supplement Table S1). This population is younger than in previous studies by our research group in geriatric wards, but at the same time shows a profile of frailty according to different variables like SPPB, hand grip, gait speed or functional measures.

## Discussion

Based on previous research showing the benefits of exercise in older adults admitted to the hospital because of medical reasons we have developed a RCT protocol for older patients with cancer. Given the relationship between both cancer and frailty (3), it makes sense that those interventions that are effective in frail patients could be beneficial in oncogeriatric patients and vice versa. This single-centre randomized controlled trial will be the first, to the best of our knowledge, to evaluate a short-term individualized multicomponent exercise program during the hospitalization period in oncogeriatric patients. A priori, the benefit could be even greater than that of the general population, but given the complexity and vulnerability of the elderly with cancer, the interventions may not have a similar response.

Although our previous research suggests that elderly patients should not be excluded from clinical trials based solely on their age, in the area of oncogeriatrics there is a wide margin of research on the effects of exercise during the hospitalization period. RCTs determine the standard of care treatment for older adults, yet they are often excluded from early phase studies. This highlights the role of geriatric oncology. Positive steps are being made, including the integration of geriatric assessment interventions for older patients with advanced cancer showing that this strategy can reduce the serious toxic effects of cancer treatment (38).

Most of the clinical evidence in oncology is based on pharmacological trials. In this study we propose the implementation of a new approach model for cancer patients, from a perspective that gets the focus of attention on function, giving it as much importance as the disease itself. As we have previously mentioned, the role of sarcopenia and muscle function is central in cancer patients, especially the elderly, therefore our intervention innovatively addresses cancer prevention. Ultimately, therapeutic priorities are diluted in geriatric patients, prioritizing quality of life over survival expectancy on many occasions (39). Proactive evaluation of functional status and appropriate interventions have been proposed by guidelines in oncogeriatric patients (40). Our intervention has not been tested among geriatric oncology patients yet; however prior studies have shown to improve functional status and in improving quality of life, and geriatric tools predicted survival and hospital utilization among older adults with hematologic malignancies (41).

The European VIVIFRAIL physical exercise prescription model that will be adopted in this study, and which has been developed by experts worldwide in the field of physical activity and frailty (and who are part of the research team), we consider being a milestone in this regard (42).

For the first time, significant progress has been made in the aforementioned individualized physical exercise prescription and its application to a population as vulnerable as the frail and cognitively impaired older adult. We bet that it can represent a significant advance in improving the functional capacity of these patients and that, as the World Health Organization says, it should be the objective of the health systems that care for these people. Our model is parallel and analogous to that posed by the concept of personalized medicine, since it individualizes the specific recommendations on exercise doses (intensity, volume, frequency) as is done with other medications.

The recruitment of this type of patient is a major challenge given the obvious differences compared to patients traditionally recruited in geriatric departments, with additional aspects beyond the purely medical issues, such as psychological aspects, the appropriate time to start complementary treatments or the interaction with baseline treatments such as chemotherapy when prioritizing the optimization of pharmacological and non-pharmacological therapies. All these factors will provide evidence that will help to update clinical guidelines related to this type of intervention in the future. At the present time, given recruitment of one-third of the initial estimate, we would have a power of almost 50% to detect as statistically significant a difference of 1 SPPB between groups.

If our hypothesis is correct, it opens the way to the modification of the hospitalization system and the current oncogeriatric management of patients with medical conditions. If we modify the current guidelines, it is likely that older adults after admission will present lower levels of functional and cognitive deterioration, predictably a better quality of life and lower consumption of health resources (lower readmissions, less institutionalization, among others).

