
### Statistical procedures

The sample size calculation was performed using the GPower v. 3.1 software, adopting a significance level of α = 5%, a correlation between pre-and post-intervention values of the Short Physical Performance Battery (SPPB) of ϱ = 0.5 and a standard deviation for the SPPB of σ = 2.5, the required sample size to have a power of 90% to detect a minimum difference of 1 point between groups in the post–pre SPPB score is 101 patients per group. Taking an expected loss of patients at follow-up of 15% into account, the final sample size required is 120 per group.

The description of the sample by the group will be conducted using statistics such as means and standard deviations or medians and interquartile ranges for the quantitative variables, and frequencies and percentages for the qualitative variables. For comparisons between groups at baseline, t-tests or Mann–Whitney U tests will be used for continuous variables, depending on normality, which will be checked for each using the Kolmogorov-Smirnov test and normal probability plots, and the chi-square test or Fisher's test will be used for categorical variables.

To determine the efficacy of the intervention in the quantitative variables, such as the SPPB, we will use linear mixed models, using time, group and time and group interaction as categorical covariates. In the case of qualitative or categorized variables (such as whether an improvement of a given magnitude between pre-and post-intervention has been achieved or not), comparisons between groups will be conducted with the chi-square test or Fisher's test, and complemented with logistic regression if additional adjustment is needed. Effect sizes between-group will be computed based on Cohen's d and the 95% confidence interval. The level of statistical significance will be 0.05. Data will be analyzed using an intention-to-treat approach with R and SPSS statistical packages.

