## Conclusions

As previously stated, we anticipate that the results obtained by this study will inform future guidelines on the management of function and cognition in oncogeriatric hospitalized patients, highlighting the importance of including a physical exercise program for reverting the deterioration that frequently occurs in these patients.

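### The stated power of almost 50% at one-third recruitment does not match the written SPPB effect and model (37–42%); the 101 per group has the same mismatch

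*Protocol article*

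**What the plan says.** Statistical procedures in the Protocol article sets out the sample size. The inputs are "a standard deviation for the SPPB of σ = 2.5" and "a correlation between pre-and post-intervention values of the Short Physical Performance Battery (SPPB) of ϱ = 0.5", and the result is a "power of 90% to detect a minimum difference of 1 point between groups in the post–pre SPPB score is 101 patients per group". The section then inflates this: "Taking an expected loss of patients at follow-up of 15% into account", the target becomes 120 per group, 240 in all. For quantitative outcomes such as SPPB, it plans linear mixed models whose listed terms are time, group and the time-by-group interaction. Baseline SPPB is not listed as a covariate, and no constraint of equal baseline means is stated. The significance level is given twice ("The level of statistical significance will be 0.05" is one place) without saying whether the test is one- or two-sided.

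The abstract says that planned recruitment will not be reached. The Discussion puts current recruitment at one-third of the initial estimate and says "we would have a power of almost 50% to detect as statistically significant a difference of 1 SPPB between groups".

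**The concern.** The Discussion figure is the only power statement for a trial of the size now in prospect, so readers will use it to weigh whatever result appears. It should describe the effect and model in Statistical procedures. In a model with only time, group and their interaction, the treatment effect at the second assessment is, with complete data, the between-group difference in change scores. The power of that contrast with the article's own SD and correlation is clearly below 50%. If the figure belongs to a different analysis, either the power is overstated or the intended analysis has not been written down. The same question then applies to the planned sample size.

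**Working it through.** **Inputs from the article:** SPPB SD 2.5; pre–post correlation 0.5; difference 1 point; 5% level; 101 evaluable and 120 recruited per group; 15% loss; recruitment at one-third of target.

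**Assumptions:** two-sided test, equal arms, complete data for the contrast, one-third taken of 240.

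**Group sizes.** 240/3 = 80, so 40 per group. After 15% loss, 40 × 0.85 = 34. One-third of 101 is 33.7, which also rounds to 34.

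**Candidate SDs.**
- Change score, which is the written time-by-group contrast: 2.5 × √(2 × (1 − 0.5)) = 2.5.
- Baseline-adjusted: 2.5 × √(1 − 0.5²) = 2.165.

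**Formulas.** Normal approximation to the required n per group: 2 × (1.960 + 1.282)² × SD² / 1². Power: Φ(1 / (SD × √(2/n)) − 1.960). The t figures use the noncentral t distribution with 2n − 2 degrees of freedom.

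**The article's own figures first.** With SD 2.165, 90% power needs 2 × 10.51 × 4.6875 = 98.5, so 99 per group (100 by t), close to the stated 101. At 34 per group the standard error is 2.165 × √(2/34) = 0.525, the ratio is 1.904, and power is Φ(−0.056) = 47.8% (46.7% by t), in line with the Discussion. One SD therefore accounts for both published figures.

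**The written model.** With SD 2.5, 90% power needs 2 × 10.51 × 6.25 = 131.3, so 132 per group (133 by t). At 40 per group the standard error is 0.559 and power is Φ(1.789 − 1.960) = 43.2% (42.4% by t). At 34 per group it is 0.606 and power is Φ(1.649 − 1.960) = 37.8% (36.9% by t). At 101 per group it is 0.352 and power is 81.1% (80.8% by t).

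| Per group | Written contrast, SD 2.5 (t) | Baseline-adjusted, SD 2.165 (t) |
|---|---|---|
| 34 | 36.9% | 46.7% |
| 40 | 42.4% | 53.2% |
| 101 | 80.8% | 90.4% |
| n for 90% | 133 | 100 |

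**Cross-checks.** The repeated-measures interaction F test gives 36.9% for 68 patients and 42.4% for 80, the same as the t calculation. Simulated change-score power was 36.6% and 42.2%; simulated baseline-adjusted power was 46.3% and 53.0%.

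**Other routes to the stated figures.**
- A one-sided change-score test gives 49.5% at 34 per group but needs 108 per group for 90%, so it does not explain 101.
- A change score with correlation 0.62 needs 101 per group and gives 46.2% at 34, but the article states 0.5.

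**Precision.** The 95% confidence interval half-width is t × SD × √(2/n): 1.11 points (40 per group) and 1.21 (34) as written; 0.96 and 1.05 baseline-adjusted.

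**The case against.** The strongest defence is that the Discussion figure is correctly calculated and agrees with the sample size, since both follow from the baseline-adjusted variance. That stands. A reader might infer an arithmetic slip in the Discussion; the figures do not support that. Changing the Discussion alone would also create an inconsistency between the two sections that does not exist now.

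A second defence is that a condensed article gives the mixed model one sentence, and that baseline handling may be settled in a fuller document. This limits certainty about what will actually be run. It does not remove the mismatch, because the article itself states the effect as the post-minus-pre difference, lists the model terms, and gives powers that those statements do not yield.

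Third, sidedness is unstated, so baseline adjustment is not the only way to approach 50% at 34 per group. That is true, but the one-sided reading fails on the 101.

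Fourth, the practical effect is limited. Any power below 50% already means that a non-significant result is likelier than not if the true effect is 1 point, and the Discussion figure describes the position at the time of writing. Both points are fair and temper the weight of the finding.

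A reader might also infer that the article keeps confirmatory conclusions despite the shortfall. It does not. The Discussion makes its claims about changing practice conditional on the hypothesis being correct, the Conclusions are worded as an expectation ("we anticipate that the results obtained by this study will inform future guidelines on the management of function and cognition"), and the article itself discloses both the shortfall and the low power.

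**Conclusion.** The point holds as an inconsistency between the stated power and the written analysis. For the effect and model in Statistical procedures, power at one-third recruitment is 42% at 40 per group or 37% at 34, about 8 to 13 percentage points below 50%. The cause lies in Statistical procedures, where the variance that reproduces 101 per group is baseline-adjusted while the stated effect and model are not. On the written model, 101 per group gives about 81% power.

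This rests on a two-sided 5% test, equal arms, complete data, one-third of 240, and the article's SD and correlation. That a baseline-adjusted variance was used is an inference from the match to both figures; the article does not say so. The finding concerns how the power is stated and how the model is specified. It is not evidence of miscalculation or of over-claimed conclusions.

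**What to change.** Correct both sections together, by one of two routes.

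(a) In Statistical procedures, specify a primary SPPB analysis that adjusts for baseline or constrains the baseline means to be equal across groups. The 101 per group then stands, and the Discussion can state about 47% power at 34 evaluable per group and 53% at 40. This needs no extra patients and gives a narrower interval.

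(b) Keep the written model. Restate the Discussion power as 37–42%, and in Statistical procedures state about 81% power at 101 per group, noting that 90% would need about 133 evaluable per group.

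Under either route, state that the test is two-sided, if that is intended, and whether the Discussion power is before or after the 15% loss. Optionally, add that the reduced trial will report its estimate with a 95% confidence interval, with an expected half-width of about 1.0 to 1.2 SPPB points. The cost is a few sentences; route (a) also changes the primary model, so it should be fixed before unblinded data are examined.
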